# Comparative Evaluation of Autologous Sticky Bone, Platelet-Rich Fibrin, and Octacalcium Phosphate–Coated Deproteinized Bovine Bone Material for the Regeneration of Human Periodontal Infrabony Defects: Protocol for a Randomized Controlled Clinical Trial

**DOI:** 10.2196/69666

**Published:** 2025-10-10

**Keywords:** autologous sticky bone, ASB, autologous platelet-rich fibrin, autologous PRF, octacalcium phosphate–coated deproteinized bovine bone material, OCP-DBBM, infrabony defects

## Abstract

**Background:**

The term *periodontium* encompasses the supporting structures around a tooth, including gingival tissue, alveolar bone, cementum, and periodontal ligament. Periodontal disorders are highly prevalent, affecting approximately 95% of the Indian population. Restoring the missing attachment apparatus is the main goal of regenerative therapy in cases of periodontal disease. The reproduction or rebuilding of damaged or lost periodontal tissue to restore the structure and functionality of the periodontium is known as regeneration. This study investigates the effectiveness of autologous sticky bone (ASB), autologous platelet-rich fibrin (PRF), and octacalcium phosphate–coated deproteinized bovine bone material (OCP-DBBM). These materials are being evaluated for their potential to enhance bone regeneration in infrabony defects, which are a significant concern in periodontal therapy. Effective bone regeneration is critical for the successful treatment of periodontal defects, as it can lead to improved clinical outcomes, including better attachment levels and reduced probing depths. This study aims to provide insights into the most effective methods for achieving these goals.

**Objective:**

We aim to assess the efficacy of ASB and autologous PRF in conjunction with OCP-DBBM in infrabony defects at 6 months after surgery with regard to radiographic bone fill, reduction in probing pocket depth, and increase in clinical attachment level.

**Methods:**

This randomized controlled clinical trial will be performed on 20 defects in patients diagnosed with stage 2 and 3 grade B periodontitis. It will be a parallel-designed study where group 1 (n=10) will be treated with ASB and group 2 (n=10) will be treated with autologous PRF and OCP-DBBM. One sitting will be required to perform the treatment, and a follow-up checkup will be done at 6 months.

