## Methods

### Recruitment

The selection of study participants was performed using well-defined inclusion and exclusion criteria to ensure uniformity and reliability of clinical outcomes. Only systemically healthy individuals diagnosed with chronic periodontitis and presenting with specific radiographic and clinical characteristics were enrolled. The inclusion criteria were designed to identify patients with distinct infrabony periodontal defects that could be assessed radiographically and managed surgically, thereby enabling accurate evaluation of regenerative outcomes. Each participant was selected after completion of initial nonsurgical periodontal therapy and demonstration of acceptable oral hygiene maintenance.

The inclusion parameters emphasized the presence of at least 1 or 2 well-defined infrabony defects with probing depth and clinical attachment loss of ≥5 mm, ensuring adequate disease severity for evaluating regenerative potential. Radiographic criteria, such as a defect depth ≥3 mm and a base positioned ≥3 mm coronal to the root apex, were essential to avoid endodontic involvement and to ensure sufficient bone support for defect containment. The requirement of a minimum of 3 mm of keratinized gingiva around the test tooth ensured soft-tissue stability and favorable surgical access.

The exclusion criteria were framed to eliminate potential confounding variables that could affect periodontal healing or regenerative outcomes. Patients with stage 4 grade C periodontitis, poor plaque control (plaque index >1), or smoking habits were excluded due to their known adverse effects on periodontal regeneration. Similarly, teeth exhibiting mobility greater than grade 2, advanced furcation involvement (class 3 or 4), or prior periodontal surgery in the same quadrant were omitted to maintain site comparability. Pregnant and lactating women were also excluded to prevent any ethical or physiological risks associated with surgical intervention and medication use.

These stringent criteria collectively will ensure that all participants meet the clinical and radiographic prerequisites for reliable assessment of treatment efficacy while minimizing biological and procedural variability (Textbox 1).

The sample size calculation was as follows:

[figure not shown]

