where α=.05, β=.1, SD in group 1 (σ1) is 0.83, mean in group 1 (μ_1_) is 0.522, SD in group 2 is (σ2) 0.044, mean in group 2 (μ_2_) is 0.42, and ratio (group 2 to group 1)=1. The total sample size required was 10 participants per group, as indicated by the calculation [13].

Inclusion and exclusion criteria for patient screening for infrabony defects.

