**Inclusion criteria**
Minimally 1 or 2 radiographically identifiable infrabony defects, with a clinical attachment loss and probing pocket depth of ≥5 mm after initial therapyDepth of intraosseous component of the defect ≥3 mmThe radiological base should be ≥3 mm coronal to the tooth’s apexThe test teeth must have at least 3 mm of keratinized gingiva

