#### Preparation of ASB

Following complete debridement, an 18G needle will be used to draw about 30 mL of venous blood from the patient’s forearm using 1 of 2 vacutainer types: (1) noncoated for autologous fibrin glue and (2) glass coated for concentrated growth factor (CGF) and alternated controlled centrifugation at 2400 rpm to 2700 rpm will be performed for 12 minutes. The autologous fibrin glue obtained will then be mixed with OCP-DBBM for polymerization, which produces a yellow, sticky bone. CGF will be mixed with the prepared sticky bone to produce the CGF–sticky bone mixture.

#### Procedure for Group 1

Complete isolation and hemostasis of the defect will be achieved. The flap will be presutured without tying the knot to allow rapid flap closure after placement of graft material. ASB will be placed into the osseous defect at the test site with light pressure until it is filled to the most coronal level of the osseous wall by raising the flap. The flap will then be coronally repositioned and sutured in such a way that the flap margin will be located 1 mm to 2 mm coronal to the cemento-enamel junction (CEJ), ensuring primary flap closure. A combination of vertical mattress and interproximal sutures (4-0 nonresorbable surgical sutures, braided black silk [Mersilk, Ethicon; Johnson & Johnson Ltd]) will be used to secure the flap in position. Slight pressure will be applied to the area with saline-soaked gauze for approximately 2 minutes to adapt the soft tissue well to the tooth surface and eliminate any space in which a clot might form and disrupt reattachment. The surgical site will be dressed with a periodontal dressing (Coe-Pak, GC Inc) on the buccal and lingual aspects.

#### Procedure for Group 2

The surgical procedure for the defect site will be identical to the procedure of the test site, except that osseous defects at group 2 sites will be packed with OCP-DBBM, and then a PRF membrane will be placed over the bone graft.

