### Calculations of Papillary Bleeding Index

Each papilla will be scored according to the aforementioned criteria. The sum of all scores will be divided by the number of papillae examined to obtain the papillary bleeding index score per person.

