### Probing Measurements

Both treatment groups will be subjected to recordings to measure PPD, relative CAL, and relative gingival margin level at 6 sites of the selected teeth. Measurements will be carried out using a UNC-15 calibrated periodontal probe (University of North Carolina) at the mesiobuccal, mesiolingual, distobuccal, distolingual, midbuccal, and midlingual points of the selected tooth. After measurement, only the deepest marking per defect will be considered for study purposes. After the fabrication of the acrylic stent, probing measurements will be recorded at baseline and 6 months postoperatively.

The UNC-15 probe will be positioned on the prepared groove of the acrylic stent. The probe will be placed with its tip at the gingival marginal level, and the distance between the gingival margin and the lower border of the stent will be measured as the relative gingival margin level. Then, the probe will be positioned at the bottom of the pocket, and the distance from the lower border of the stent to the bottom of the pocket will be noted as the relative CAL. PPD will be measured by subtracting the relative gingival margin level from the relative CAL. The width of keratinized gingiva will be calculated from the lowest point of the mucogingival junction to the crest of the gingival margin using the UNC-15 probe.

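### The unit of randomisation and analysis is inconsistent (20 defects, or 10 participants per group); if a patient gives two defects to the same arm, the planned tests understate the standard error

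*Protocol article*

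**What the plan says.** Two units of count appear in the protocol article.

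- **Defects.** The abstract (Methods) says the trial "will be performed on 20 defects in patients diagnosed with stage 2 and 3 grade B periodontitis" and gives no number of patients. It continues: "It will be a parallel-designed study where group 1 (n=10) will be treated with ASB". The unit of that n is not named.
- **Participants.** The sample size paragraph under Recruitment concludes: "The total sample size required was 10 participants per group".

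Eligibility is open to more than one defect per patient. Textbox 1 asks for "Minimally 1 or 2 radiographically identifiable infrabony defects", and the Recruitment text for the "presence of at least 1 or 2 well-defined infrabony defects". Both are worded as a minimum, with no cap.

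Outcomes and treatment are described partly by defect or site. Under Probing Measurements, "only the deepest marking per defect will be considered for study purposes". Under Procedure for Group 2, "osseous defects at group 2 sites will be packed with OCP-DBBM". By contrast, the plaque and bleeding indices are computed by patient; the bleeding scores are averaged "to obtain the papillary bleeding index score per person".

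The Statistical Analysis section names ANOVA or Kruskal-Wallis for the comparison between groups and mentions no allowance for defects within a patient. No passage says whether patients or defects are randomised, or which defect is the study defect when a patient has two.

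**The concern.** The two counts agree only if every patient contributes exactly one defect, and the article never says so. Under the stated criteria, 20 defects could come from 20 patients or from as few as 10 patients with two defects each.

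Two defects in one mouth share the patient's healing response and oral hygiene and, in this trial, a product made from the same patient's blood. Their outcomes are likely to be correlated. ANOVA and Kruskal-Wallis treat them as independent. If both defects sit in the same arm, which is the natural reading of a parallel design, the arm mean varies more than the test allows for. P values are then too small and confidence intervals too narrow, and 10 defects carry less information than the 10 independent units in the sample size statement.

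The per-person indices have a smaller version of the same problem. In an analysis by defect, a two-defect patient's plaque score would be counted twice, or would belong to no single arm if the defects were split.

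**Working it through.** **Inputs from the article.** n = 10 per group; one or two defects per patient; tests that assume independence. For the sample size: α = 0.05, β = 0.1, means 0.522 and 0.42 (difference 0.102), SDs 0.83 and 0.044.

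**Assumptions.** The article gives neither an intraclass correlation (ICC) between defects in one patient nor a count of two-defect patients. I take ICC from 0.1 to 0.7 and consider two or five two-defect patients among the 10 defects in each arm.

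**Step 1. The plan's own figure.** n per group = (SD1² + SD2²)(z₀.₉₇₅ + z₀.₉)² / difference². The printed inputs give (0.6889 + 0.0019) × 10.507 / 0.0104 ≈ 698, not 10. If SD1 were 0.083 (an assumed decimal slip), the formula gives 8.91, so 9, and the t-based version gives 10. That discrepancy is a separate matter. What counts here is that either version treats the units in each group as independent, with no clustering term.

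**Step 2. Variance of an arm mean.** With k two-defect patients among 10 defects in an arm, both defects in that arm, the variance relative to independence is (10 + 2k × ICC)/10. For k = 5 this is 1 + ICC. The true standard error exceeds the independence standard error by the square root of this ratio:

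- k = 2: √1.04 = 1.02 at ICC 0.1, rising to √1.28 = 1.13 at ICC 0.7.
- k = 5: √1.10 = 1.05 at ICC 0.1, rising to √1.70 = 1.30 at ICC 0.7.

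**Step 3. Type I error.** I simulated the two-group t test (equivalent to a two-group ANOVA) on 10 against 10 defects with no true difference, normal outcomes and 100,000 runs per setting, at a nominal 5%:

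| ICC (assumed) | 2 two-defect patients per arm | 5 two-defect patients per arm | Defects split: 10 patients, one defect in each arm |
|---|---|---|---|
| 0.1 | 5.4% | 6.1% | 3.9% |
| 0.2 | 6.0% | 7.6% | 3.0% |
| 0.3 | 6.5% | 8.8% | 2.4% |
| 0.5 | 7.6% | 11.8% | 1.0% |
| 0.7 | 8.6% | 15.0% | 0.2% |

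With one defect per patient the ratio in step 2 is 1 and the test holds its level. In the split column the true standard error is √(1 − ICC) times the naive one, from 0.95 down to 0.55, so the naive standard error is too large.

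**Step 4. Information.** With five two-defect patients per arm, the effective number per arm is 10/(1 + ICC): 8.3 at ICC 0.2 and 6.7 at ICC 0.5. Matching 10 independent units would take 10 × (1 + ICC) = 12 or 15 defects per arm.

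**The case against.** The counts need not conflict. Twenty defects and 10 participants per group agree exactly if each patient gives one defect, and some wording is singular (the study tooth, the selected quadrant). The defect criterion can be read as an eligibility threshold, and no passage says that two defects per patient will be treated or analysed. The article is condensed, and handling of multiple sites is often left to a fuller document. The wording about tests is also generic, and the plaque and bleeding indices are not among the listed primary or secondary outcomes.

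Much of this stands. It rules out two stronger readings that a reader might infer:

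- **That the planned tests will give standard errors that are too small.** This needs patients to contribute two defects and both to fall in one arm. The article states neither, and split defects would push the error the other way.
- **That power falls well below 90%.** Five patients per arm, analysed at patient level, would have 75%, 69% and 64% power at ICC 0.3, 0.5 and 0.7. But this sets aside the stated 10 participants per group and uses an SD of 0.083 where 0.83 is printed. If 10 patients per group each gave two defects, the same calculation gives 98%, 96% and 94%. The unadjusted test would still reject a true null about 9% to 14% of the time.

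The objection does not remove the inconsistency. The article counts in two units, admits two-defect patients and keeps data by defect. Filling 20 defects from two-defect patients would follow the abstract as written. A later analysis document can correct the tests, but it cannot supply patients who were not recruited.

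**Conclusion.** The concern holds in conditional form. The unit of randomisation and analysis is inconsistent between the abstract, the sample size paragraph, the eligibility criteria and the probing section, and the named tests are valid only if each patient contributes one defect.

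If two-defect patients enter with both defects in one arm, the nominal 5% test has a type I error of about 5.4% to 8.6% (two such patients per arm) or about 6% to 15% (five per arm). These ranges rest on the assumed ICC of 0.1 to 0.7, normal outcomes and 10 defects per arm; they do not depend on the printed SDs. As written, a reader cannot tell whether the P values would be too small, correct or too large. That should be settled before the primary comparison is analysed.

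**What to change.** Reconcile the abstract, the sample size paragraph and Textbox 1 by making the patient the unit of randomisation and of the primary analysis: 20 patients, 10 per group, one index defect each.

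- **Index defect.** Choose it by a fixed rule that uses only baseline data and is blind to outcome, among defects that pass the intrasurgical eligibility check described under Debridement and Root Surface Management.
- **Patients already treated.** Recruitment began in June 2025 and data are due by February 2026. With six months of follow-up, the last surgery would fall at about August 2025, before the article appeared in October 2025. The rule must therefore also be applied, before analysis, to patients already treated.
- **Fewer than 20 patients.** If fewer than 20 patients supply the 20 defects, analyse patient means or use a patient-level random effect, and restate the effective sample size and power.
- **Second defects.** Use their data only in a supportive mixed model with a patient-level random effect. Which treatment a second defect receives is for the investigators to state.

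The cost is small if each patient already gives one defect: a change of wording plus the selection rule. The downside is that second defects do not count toward the 20. If two-defect patients have already been counted, the trial must recruit more patients or report the smaller effective sample size.

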**Results:**

Recruitment procedures started in June 2025. All data are anticipated to be collected by February 2026. Full trial results are anticipated to be analyzed and submitted for publication by March 2026. The study’s anticipated end date is March 2026.

**Conclusions:**

Both treatment approaches are expected to lead to notable gains in periodontal health and bone regeneration. The primary outcome, radiographic bone fill, and the secondary outcomes, clinical attachment level gain and probing pocket depth reduction, are critical indicators of treatment success.

**Trial Registration:**

Clinical Trials Registry-India CTRI/2024/06/069603; https://www.ctri.nic.in/Clinicaltrials/pmaindet2.php?EncHid=MTAzODk0&Enc=&userName=

**International Registered Report Identifier (IRRID):**

PRR1-10.2196/69666

## Introduction

### Background

Disease problems affecting the periodontium are referred to by the word *periodontium*, which describes the supporting structure surrounding a tooth and is made up of the gingival tissue, alveolar bone, cementum, and periodontal ligament. The damaging, irreversible, chronic inflammatory disease that follows gingivitis is called periodontitis. As a result, the bacteria are more likely to enter the surrounding tissues and periodontium. This initiates the host defense system against the microbes that are invading the area [1].

Periodontal disorders, which impact 95% of the Indian population, are one of the most common oral ailments. Periodontitis frequently results in infrabony defects with periodontal pockets, which are the anatomical consequences of plaque spreading apically in the course of periodontitis. “Regeneration of periodontal attachment will become the major goal of regenerative therapy when periodontal disease results in the loss of the attachment apparatus” [2].

Regeneration has been defined as “the reproduction or reconstitution of a lost or injured part to restore the architecture and function of the periodontium. The aim of regenerative periodontal therapy is to restore the structure and function of the periodontium” [3].

Numerous regenerative periodontal therapies have been developed over the past 20 years with the goal of replacing lost tooth-supporting tissues, such as the cementum, alveolar bone, and periodontal ligament [4]. The various regenerative materials used are guided tissue regeneration, enamel matrix derivative, bone grafts like autografts, allografts, and xenografts, matrix-based scaffolds**,** and synthetic materials like demineralized freeze-dried bone allograft (DFDBA), anorganic bovine bone, hydroxyapatite, and tricalcium phosphate. These are osteoconductive in the repair of deformities, acting as a mechanical scaffold for the formation of new bone [5].

When it comes to periodontal graft materials, autograft is regarded as the best. However, patients often resort to alternative periodontal treatment approaches to avoid a surgical donor site and associated complications [6]. Hydroxyapatite, octacalcium phosphate, and DFDBA are a few of the several synthetic materials, xenografts, and allografts that are available and widely used as regeneration materials [7].

Both osteoconductive and osteoinductive qualities are present in the new gold standard for xenografts, macropore octacalcium phosphate–coated deproteinized bovine bone.

This is made from a 100% bovine cancellous bone substitute. Because graft bone materials have a high osteoconductivity, they aid in the proliferation of osteogenic cells and microvessels, which in turn stimulate the formation of new bone [8].

To facilitate the successful regeneration of damaged periodontal tissues, autologous sticky bone (ASB) was introduced as an alternative. ASB is defined as a physiologically solidified bone graft that is embedded in the fibrin network. Strong interconnection of particle bone powders by the fibrin network prevents scattering, even when shaken with a cotton plier. Sticky bone offers many benefits: (1) it can be shaped to suit virtually any kind of bony defects; (2) it prevents the grafted bone from moving; (3) no biochemical additives are needed to maintain the volume of augmentation during the healing period, thereby minimizing the need for block bone and titanium mesh; (4) fibrin accelerates bone and soft tissue regeneration by entrapping platelets and leukocytes that release growth factors; and (5) fibrin interconnection minimizes soft tissue ingrowth into the sticky bone graft [9].

One of the newest developments in regenerative surgery is the use of platelet concentrates for in vivo tissue engineering applications: the first two are platelet-rich fibrin (PRF) and platelet-rich plasma. Platelet concentrates, a concentrated solution of growth factors produced from platelets, are applied as a bioactive surgical adjuvant to facilitate the healing of wounds [10].

As radiographs can identify the quantity and type of damage to the alveolar bone, they play a significant role in periodontal diagnostics. Further research comparing radiographs to presurgical measures found that “bone loss can be underestimated by 1.5 mm, with considerable differences in examiners’ interpretations” [11].

Computed tomography scans have been explored for their potential in highly accurate 3D image alignment. However, they have limitations, including significant radiation exposure and the bulkiness and expense of the equipment [12]. Cone-beam computed tomography (CBCT) has recently emerged as a viable technique in dentistry, offering a lower-cost alternative to traditional computed tomography while still producing high-quality pictures and exposing patients to less radiation.

Therefore, this study will be carried out to evaluate the effectiveness of ASB and autologous PRF along with octacalcium phosphate–coated deproteinized bovine bone material (OCP-DBBM) in the treatment of human infrabony defects.

